#### Additional Analyses

Exploratory analyses will examine potential moderators and predictors of treatment response (e.g., age, sex, baseline fatigue severity, autonomic function). Linear or logistic regression models will be employed, including interaction terms where appropriate. These analyses are hypothesis-generating; results will be interpreted cautiously and without correction for multiplicity, and effect sizes with 95% CIs will be provided. If substantial missing data is observed, multiple imputation will be undertaken as a sensitivity analysis. Consistent with the intention-to-treat principle, all randomized participants will be included in primary analyses; while the per-protocol analysis will be restricted to those attending ≥ 70% of sessions. Adherence rates may be incorporated as covariates in exploratory models.

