## Abstract

**Background/Objectives:** Myalgic Encephalomyelitis/Chronic Fatigue Syndrome (ME/CFS) and Post-COVID Syndrome (PCS) are chronic conditions that share relevant pathophysiological mechanisms. Conventional rehabilitation programs have often been associated with patient dissatisfaction and frequent adverse events (AEs), highlighting the need for safer and more effective clinical approaches. This study aims to compare the effects of a telerehabilitation program based on conscious movement with those of conventional low-intensity exercise in individuals with ME/CFS or PCS. **Methods:** This is a prospective, single-blind, three-arm, parallel, superiority randomized clinical trial. A total of 147 participants (aged 18–70) with ME/CFS or PCS will be recruited and randomly assigned to one of three groups: (a) conscious movement; (b) low-intensity exercise; or c) usual care. All interventions will be delivered via telehealth over 12 weeks, with weekly 45-min sessions combining health education and individually tailored exercises. Participants will be encouraged to practice daily using the provided materials. Adherence rates and potential AEs will be recorded. The primary outcome is the total score on the 14-item Chalder Fatigue Scale at 12 weeks (post-intervention). Secondary outcomes include heart rate variability, functional performance, pain intensity and interference, mental health, interoceptive awareness, quality of life, sleep quality and fear of movement. Measurements will be collected at baseline, post-intervention, and at 3-month follow-up. **Discussion:** Recent evidence suggests that both autonomic and cognitive activity modulate immune function. Conscious movement, which integrates exercise with interoception and mindfulness-based strategies, may provide greater benefits than low-intensity exercise alone. Study limitations should be considered when interpreting the results. **Trial registration:** Registered at ClinicalTrials.gov on 15 May 2025 (NCT06978582). Protocol version 4 (29 September 2025). Ethics Committee code: 2025-0180.

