#### 2.10.4. Criteria for Discontinuing or Modifying Allocated Interventions

Participants may pause or modify sessions at any time according to pacing principles. Therapists may recommend temporary pauses or adjustments based on symptoms. No cross-over between study arms will be permitted. The principal investigator (PI) will decide on discontinuation if safety concerns arise. Withdrawals will be respected without requiring justification. Temporary interruptions due to intercurrent illness or symptom flare will be permitted, with resumption when appropriate. Enrollment in other clinical trials will not be allowed. Any relevant changes in medical treatment will be documented but will not necessarily lead to withdrawal unless recommended by a physician. In the event of AEs, participants will be offered an individual videocall to address causes and adjust the intervention accordingly. More specific details are included in Supplementary File S2.

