#### 2.11.1. Primary Outcome

The primary outcome is the total score of the CFQ-14 (Spanish version) at 12 weeks (post-intervention). The CFQ-14 measures perceived physical and mental fatigue over previous weeks on a 4-point Likert scale (0 = “never”, 1 = “sometimes”, 2 = “often”, 3 = “always”), total score 0 to 42, with higher scores denoting greater fatigue. The Spanish version of the CFQ-14 has demonstrated adequate reliability and validity [45]. 

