### 2.14. Statistical Methods

Statistical analyses will be conducted using IBM SPSS Statistics, version 26.0 (IBM Corp., Armonk, NY, USA), under an intention-to-treat framework. A complementary per-protocol analysis will include participants achieving ≥ 70% adherence. Baseline characteristics will be summarized as mean (standard deviation) or median (interquartile range, Q1–Q3) for continuous variables, and as frequencies (%) for categorical variables. Between-group comparability at baseline will be examined using chi-square or Fisher’s exact tests for categorical variables, and one-way analysis of variance (ANOVA) or Kruskal–Wallis tests for continuous variables, according to distributional assumptions. Normality will be assessed with the Shapiro–Wilk test and by visual inspection of histograms and Q–Q plots to identify skewness, kurtosis, or outliers. When appropriate, homogeneity of variances will be verified with Levene’s test.

The primary outcome (CFQ-14 total score at 12 weeks, post-intervention) will be analyzed using linear mixed-effects models (LMMs) with fixed effects for group, time, and their interaction (group × time), and random intercepts to account for within-subject correlation. This approach accommodates repeated measures and missing data under a missing-at-random assumption [55]. Estimated marginal means with 95% confidence intervals (CIs) will be reported. Effect sizes will be presented as standardized mean differences (Cohen’s d) and partial eta squared (η^2^).

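### The one missing-data check named is multiple imputation, run only if missingness looks substantial; by default it shares the primary model's missing-at-random assumption and does little to test symptom-driven dropout

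*Protocol article*

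**What the plan says.** Section 2.14 (Statistical Methods) analyses CFQ-14 at 12 weeks with a linear mixed model (group, time, group by time, random intercept) and says that the model "accommodates repeated measures and missing data under a missing-at-random assumption". Under Additional Analyses, "all randomized participants will be included in primary analyses", and the provision for missing data is: "If substantial missing data is observed, multiple imputation will be undertaken as a sensitivity analysis". The article gives no threshold, no imputation model and no missingness mechanism for that step. The other secondary analysis there concerns adherence, not missing outcomes: "the per-protocol analysis will be restricted to those attending ≥ 70% of sessions".

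Four other places bear on the point:
- Abstract: "Measurements will be collected at baseline, post-intervention, and at 3-month follow-up". CFQ-14 is therefore not measured between baseline and week 12.
- Section 2.7 (Sample Size): 20% dropout is allowed for.
- Section 2.10.4: "Withdrawals will be respected without requiring justification".
- Section 2.11.4: a daily diary records adverse events and post-exertional exacerbations. Its entries are to inform safety reviews and sensitivity analyses, but the section does not say which sensitivity analyses.

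**The concern.** A sensitivity analysis should vary the assumption on which the main result rests. A likelihood-based mixed model and standard multiple imputation both assume that, given the observed data, those with missing scores resemble those without. Using the same variables, they give nearly the same answer, so their agreement is not evidence that the assumption holds.

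The assumption is open to doubt in this trial. The Introduction names post-exertional malaise and symptom flares as the potential adverse events, and the trial's own hypothesis is that these differ between the two exercise programs. If one arm loses participants who got worse, its 12-week mean is estimated from those who did better, and a default imputation would appear to confirm it. The bias could favor either arm.

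The trigger adds a second weakness. Whether the check is run depends on a judgement about an undefined word, made once the data are in view.

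**Working it through.** **Plan's own figure.** Inputs from section 2.7: difference 6, variance 56.5, one-sided alpha 0.05, power 80%, design effect 2, dropout 20%.
- n per group = 2 × 56.5 × (1.645 + 0.842)² / 6² = 19.41.
- 19.41 × 2 / 0.80 = 48.5, so 49 per group and 147 in total, as stated. The point raised here does not change this number.

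**Size of the possible bias.** Let delta be the number of points by which dropouts are worse at 12 weeks than missing at random predicts. Delta is an assumption; the documents give no value.
- Bias in an arm's mean = dropout proportion × delta.
- At 20%: 0.20 × 4 = 0.8 and 0.20 × 6 = 1.2 points, or 13% to 20% of the 6-point target.
- With 10% dropout in one exercise arm and 30% in the other (also assumed) and the same delta in both, the contrast is biased by (0.30 − 0.10) × 4 to 6 = 0.8 to 1.2 points.
- The bias cancels only if dropout proportion × delta is equal in the two arms.

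**Would it change a conclusion?** Completers per arm = 49 × 0.80 = 39.2. Unadjusted standard error = √56.5 × √(2/39.2) = 1.70. The smallest significant difference is 1.96 × 1.70 = 3.33 points (two-sided 0.05), or 4.06 with Bonferroni for three pairs. If only the mind–body arm's dropouts are shifted and the standard error is held fixed, the tipping delta is (estimate − smallest significant difference) / 0.20:

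| Estimate under missing at random | Tipping delta, two-sided 0.05 | Tipping delta, Bonferroni for 3 pairs |
|---|---|---|
| 6 points | 13.4 | 9.7 |
| 5 points | 8.4 | 4.7 |
| 4 points | 3.4 | already not significant |

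For a delta of 4 to 6, an estimate of 6 falls to 5.2–4.8 and remains significant. An estimate of 4 falls to 3.2–2.8 and does not.

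**Would default imputation reveal the problem?** A simulation compared the approaches (1,500 runs, 49 per arm, SD √56.5, about 20% missing in each arm). Dropout in the mind–body arm depended on the participant's own week-12 fatigue; in the comparator it was random. Assumptions not in the documents: baseline to week-12 correlation 0.5, logistic dropout slope 1.2 per SD, and a diary score equal to the outcome plus noise of half its SD, available for every dropout. Baseline-adjusted regression on completers stands in for the mixed model.

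| Analysis | True effect −6 | True effect 0 |
|---|---|---|
| Full data, nothing missing | −5.93 | 0.07 |
| Missing-at-random analysis | −7.06 | −1.06 |
| Multiple imputation from baseline CFQ-14 | −7.09 | −1.09 |
| Multiple imputation adding the diary score | −6.25 | −0.25 |

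Against the full-data result, the primary-type analysis overstates the benefit by 7.06 − 5.93 = 1.13 points and baseline-only imputation by 7.09 − 5.93 = 1.16. The check agrees with the result and shares its error. With the diary score the excess falls to 6.25 − 5.93 = 0.32. Equal dropout rates gave no protection, because the causes differed. An error of 1.13 points at 20% missing corresponds to a delta of 1.13 / 0.20 = 5.7, within the 4 to 6 used above.

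**The case against.** The strongest case on the other side has four parts.

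- **The article is condensed.** Imputation models, numeric triggers and tipping-point runs are normal content for an analysis plan, which may exist. This stands for anything the article merely leaves out: a reader might infer that no analysis departing from missing at random is planned anywhere, and the document does not support that. It does not rescue what the article states, namely a conditional trigger and a check that by default leaves the primary assumption untouched.
- **Missing at random is stated only for the mixed model.** This stands. For the imputation it is an inference from the unqualified term, and imputation can be run with a delta shift.
- **The diary.** A reader might infer that the planned check cannot reveal symptom-driven dropout. That is too strong: section 2.11.4 intends diary entries for sensitivity analyses, and in the simulation a diary-type score removed most of the bias. But the article does not link the diary to the imputation, the simulated gain assumed diary data for every dropout, and worsening after entries stop would stay unseen.
- **Withdrawal is not the same as a missing score.** Flare-related pauses, a two-week questionnaire window and retention measures all work against missing data, and both exercise arms use the same pacing limits. This is fair. The deltas and the 10% versus 30% split are assumptions, and 0.8 to 1.2 points is less than one standard error. A reader should not conclude that the primary result will be biased, only that the named check would be poorly placed to say so.

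The trial's safety aim is separate and descriptive, and is not at issue here.

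**Conclusion.** The point holds in a limited form. The one missing-data sensitivity analysis that the article names is conditional on an undefined amount of missingness. Unless it draws on the diary or a delta shift, it repeats the primary model's assumption using almost the same information, so it does little to test dropout driven by symptoms.

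The practical stake is moderate. For assumed deltas of 4 to 6 points and 20% dropout, the shift is 0.8 to 1.2 points. A result at the planned 6 points would survive; a result near 4 might not, and the default check would not distinguish the two cases. These figures rest on the assumed deltas, a shift in one arm only, and an unadjusted standard error of 1.70. Adjustment for baseline would reduce that error and move the tipping points outward.

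**What to change.** Replace the conditional sentence under Additional Analyses with a commitment along these lines:

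> Whatever the amount of missing data, CFQ-14 at 12 weeks will be re-analysed by multiple imputation, carried out separately by arm, with diary post-exertional malaise entries and session attendance (exercise arms) as auxiliary variables. Imputed values will be shifted by 0 to +6 points, extended until the result tips, with the shift applied separately by arm, including to one active arm alone. The tipping point will be reported.

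The zero-shift run shows what the diary and attendance add; the shifted runs test the assumption itself. Reference-based imputation from usual care is optional: it answers a different question and is not needed to repair this point.

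The cost is a little extra analysis and some post-imputation syntax in SPSS, or the use of R. No new data are needed and the sample size stays at 147.

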### 2.15. Oversight and Monitoring

The PI will oversee trial supervision, coordinate all project activities, monitor progress, and implement corrective actions as needed. The research team will serve as the coordinating center, ensuring adherence to the protocol and maintaining high-quality trial conduct. As no serious AEs are anticipated, no independent data monitoring committee will be established. The PI will be responsible for ensuring trial safety and integrity, and will fully cooperate with any auditing procedures, providing all requested documentation. In the event of a major AE, the PI will promptly contact the participant’s treating physician and the Institutional Ethics Committee to determine the appropriate course of action.

Although no major protocol modifications are expected, any amendments will be first submitted to and approved by the Institutional Ethics Committee before implementation. Participants will be informed of any changes affecting their involvement, and updated study materials (e.g., information sheets) will be provided when necessary.

### 2.16. Dissemination Plans

Study findings will be communicated to participants at the end of the trial. Results will also be disseminated to the scientific and clinical community through presentations at national and international conferences and publications in high-impact, open access journals. Reporting will follow transparent research practices.

The full study protocol and data collection materials will be made publicly available to promote transparency and reproducibility. De-identified datasets and analysis code will be deposited in the institutional open-access repository (https://idus.us.es/home, accessed on 12 October 2025) under a persistent identifier and will remain accessible without time restriction. Source data containing personal information will be securely stored on university servers for 3 years after study close-out and will then be deleted or irreversibly anonymized.

## 3. Discussion

Although the exact pathophysiological mechanisms underlying both ME/CFS and PCS remain unclear, current evidence suggests a central role of the immune system. Persistent systemic inflammation and immune dysregulation may contribute to dysfunction across multiple systems [57,58,59]. Increasing research highlights complex interactions between cognition, the nervous system, and immune function [60,61,62]. Stress and cognitive-emotional states activate the HPA axis and the autonomic nervous system, altering glucocorticoid release and sympathetic–parasympathetic balance, which in turn modulates cytokine production and immune cell activity [63]. In addition, learning and conditioning processes can modify immune responses, underscoring the bidirectional links among brain, behavior, and immunity [64,65]. These findings indicate that therapeutic approaches targeting not only physical but also cognitive, autonomic, and interoceptive domains may achieve broader benefits. In this context, interventions designed to enhance bodily awareness, regulate autonomic activity, and reduce maladaptive cognitive patterns, such as MBE, may complement conventional rehabilitation and promote sustained improvements.

The present trial protocol operationalizes this rationale through a structured telerehabilitation exercise program, offering a feasible and accessible alternative to traditional in-person interventions. By eliminating barriers related to transportation, fatigue, and travel demands, the proposed MBE program is expected to facilitate adherence and reduce the economic burden for both patients and healthcare systems. The telerehabilitation format aligns with current trends in digital health, representing a scalable strategy for implementation in public healthcare settings. In Spain, as in many other countries, adults diagnosed with ME/CFS or PCS often face substantial barriers to adequate care, beginning with difficulties obtaining an accurate diagnosis under accepted clinical criteria, and are compounded by the lack of specialized, coordinated healthcare units. All this leaves patients to navigate fragmented services with limited professional guidance and support [39,40,66], which further exacerbates the burden of living with limited energy and highly disabling symptoms. A structured telerehabilitation program that combines exercise, self-management strategies, and education, with a consistent follow-up from a coordinated multidisciplinary team, could therefore be highly meaningful from a clinical perspective. Even modest improvements in functional capacity and symptom management could translate into substantial changes in quality of life, while addressing the unmet needs of an often-unserved population. In line with emerging research directions [67,68], this study proposes a symptom-titrated telerehabilitation approach that dynamically adjusts exercise load through clear, structured, and comprehensive pacing strategies tailored to individual’s clinical response. The MBE program has been designed to address key limitations of previous telerehabilitation programs and provide a truly personalized care model for patients with ME/CFS and PCS. Therefore, the trial findings may help shape future clinical guidelines and inform public health strategies into standard management of CFS/ME and PCS

Nevertheless, this approach presents inherent limitations. In line with other telemedicine trials, participation requires stable internet access and basic digital literacy, which may restrict the generalizability of findings [69]. Moreover, individuals with cognitive impairments may face challenges engaging with online content, scheduling videoconferences, or using digital applications [50]. These issues may be further complicated when digital tools such as the Welltory app are not available in the participant’s native language. Online assessments may also limit the precision of certain outcome measures compared with face-to-face evaluations. Although all instruments in this trial have been validated, some may not achieve the same accuracy as gold-standard methods available in onsite settings. Biological sampling is also precluded in an online clinical trial. Self-report outcomes are susceptible to expectation and recall bias; we aim to mitigate through triangulation with objective and observer-rated measures. The absence of in-person group dynamics may further reduce potential psychosocial benefits derived from peer interaction and shared experiences, which are commonly observed in traditional rehabilitation environments [70]. These limitations should be carefully considered when interpreting trial results and planning future iterations of the interventions. 

Despite these limitations, this randomized controlled trial will represent a significant advance in three key areas. First, rigorous monitoring of AEs and systematic implementation of pacing strategies are essential to minimize the risk of PEM. Future studies should continue prioritizing safety to ensure that rehabilitation protocols for ME/CFS and PCS are both effective and acceptable for patients [13,71]. Second, this trial will evaluate the impact of integrating an MBE approach within a telerehabilitation format, with a direct comparison with a conventional exercise program commonly used in this population. Third, it addresses a critical gap in the management of ME/CFS and PCS by testing a scalable, low-cost, safe, and patient-centered intervention. If the intervention proves clinically effective, the findings could inform health policy and support the integration of supervised telerehabilitation into standard care pathways for adults with ME/CFS or PCS.

## 4. Conclusions

This trial aims to examine the effects of a 12-week mindful exercise telerehabilitation program compared to conventional exercise and usual care in individuals with ME/CFS and PCS. Beyond testing feasibility and clinical outcomes, this study seeks to elucidate whether an interoceptive, symptom-titrated approach can support safer and more sustainable physical activity engagement.

Findings from this trial may help refine personalized rehabilitation strategies and inform the integration of telerehabilitation into routine clinical pathways for ME/CFS and PCS. By providing a structured, evidence-based model of remote delivery, the protocol could serve as a foundation for future multicenter or cross-national collaborations and guide health policy decisions toward broader access to individualized, home-based rehabilitation options.

## 5. Trial Status

The trial is ongoing and is currently during the recruitment phase. Recruitment was initiated on 1 July 2025, and is expected to be completed by the end of January 2026. 

Protocol version 4 (29 September 2025). The trial was registered at ClinicalTrials.gov (NCT06978582) on 15 May 2025, and the most recent update was posted on 29 September 2025. 

## Figures and Tables

**Figure 1 healthcare-13-03062-f001:**
[figure not shown]
Flow diagram. Different background colors represent the different groups.

